#### Recruitment plans.

We will utilize existing connections with various community-based weight management programs across the selected area to ensure recruitment amount is achieved. Retention will be promoted with bi-weekly contacts between Visits 1–3, and monthly contacts between Visit 3 and 4. We will promote shorter visits for Visti 2–4 by providing surveys ahead of time for participants to complete via secure weblink, thus shortening time for weight, EMA and saliva set up at the visit. All available data will be sought in the case of discontinuation after Visit 1, with the priority of weight, EMA, surveys, and then saliva collection.

#### Data management plan.

All participants will be given an ID as part of the screening process. This ID will be stored on a secure database at the University of Kansas Medical Center. Only approved project staff will have access of the server. At each major time point (week-0, 6-weeks, 12-weeks, and week-26), we will collect other participant data including anthropometry (weight and height), accelerometry, questionnaires related to participant behaviors, stress, and stress-related states. Program attendance data will be collected after Visit 4. These values will be reported as tabular data and stored in a secure electronic data capture system. All subject-level clinical data will be preserved and shared. Shared data will be deidentified, and the original data will be maintained at the investigator’s institution. Completed salivary tubes will be frozen until analysis and stored at a biospecimen freezer at the local site. This data will be processed within 1-year of collection to calculate salivary cortisol, and remaining biospecimen will not be stored.

Missing data and data quality will be assessed throughout the study, including REDCap validation rules, double data entry of values (e.g., height and weight), reviewing participant salivary collection logs, and periodic review of study records. For EMA, participants are contacted multiple times during their use period to ensure compliance and any technical issues that may impact obtaining data. For accelerometry, device non-wear periods and implausible values will be identified through reviewing device wear logs and routine quality control procedures of devices. During analysis, we will examine patterns of missing data. If appropriate, mixed models will be used; these models are robust to incomplete repeated measures under a missing-at-random assumption. Further, sensitivity analyses may be considered to evaluate the impact of missing data on study findings.

#### Current progress.

The current study began recruitment on March 7^th^, 2025. As of January 2026, we have enrolled nine participants, six participants have completed their week-6 visit, and four have completed their 3-month visit. One person was lost to follow up after their 3-month visit. No adverse events have been reported. We anticipate concluding recruitment in 2026, with data collection completed by February 28^th^, 2027. Descriptive and final results are expected to be published in the year 2027.

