### Participants, eligibility, and recruitment

This study seeks 50 individuals who are newly enrolled in a community-based weight loss program centered in a metropolitan area of a Midwest state. Participants will be recruited from an existing 6-month-long community-based weight management program hosted by the University of Kansas Medical Center, local Diabetes Prevention Programs and other behavioral weight loss programs in the local area that may range from 6 to 12-months long. These weight management programs typically include trained health educators, 1-hour weekly video meetings, group peer support, structured nutrition plan (low calorie diet), personalized activity recommendations, and behavior change modifications [15]. Prospective participants will be recruited at their initial consultation or orientation visit for their behavioral weight loss program. Flyers will also be presented to participants at their initial visit. Measures were planned to coincide with initial enrollment (week-0), early weight change (week-6), and later weight change measures (week-12, week-26).

To be included, participants must be newly enrolled or plan to enroll in a community-based weight management program, must be over 18 years of age, have body mass index (BMI) ≥30 m/kg^2^, own a smartphone and be willing to download the mobile application to receive text messages [16]. Participants who chose to cease their community-based weight management program involvement after enrolling in the INSTANT study can still participate in later assessments, improving upon past studies which only included individuals who completed their program [17,18]. Indeed, stress may impact continued engagement in a weight management program. Participants will be excluded for being currently prescribed FDA-approved medications for weight loss, treatment for a medical condition that could affect body weight, or impacting stress levels (e.g., antidepressants), a current psychological condition that is untreated, hospitalization for a psychological condition within the past 12-months, or not being on a stable dose of treatment for at least 6-months. Other exclusion criteria are not being fluent in writing or speaking the English language, mobility limitations so they are unable to perform physical activity, and a family member who was previously enrolled or is currently enrolled in the study.

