#### Follow-up visits (week-6, week-12, week-26).

At Visit 2–4, participants will have their height and weight measured, complete questionnaires, be provided the 5-day salivary cortisol collection kit, have an accelerometer fitted to their wrist to wear for 14 days and have the EMA app reinstalled on their phone to conduct the same EMA questions for 14-days. To reduce questionnaire burden in follow up visits, participants were given the option to complete questionnaires 1-week ahead of the visit using an online tool (REDCap). Harms and adverse events will be assessed at each visit. Study assessments are low-risk, thus we anticipate few study-related harms.

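### At the observed accrual rate, 50 participants with week-26 follow-up cannot be reached by 28 February 2027; the article's own figures project about 14 to 16

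*Protocol article*

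**What the plan says.** All references are to the protocol article.

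- **Target** (Participants, eligibility, and recruitment): "This study seeks 50 individuals who are newly enrolled in a community-based weight loss program". Sample size and power calculation ties n = 50 to 0.80 power, with effect size 0.3, alpha 0.01 and up to five predictors.
- **Progress** (Current progress): "The current study began recruitment on March 7^th^, 2025" and "As of January 2026, we have enrolled nine participants".
- **Timeline** (Current progress): "We anticipate concluding recruitment in 2026, with data collection completed by February" 28, 2027. No month is given for the close of recruitment.
- **Follow-up per participant**: weight is measured up to week 26 ("later weight change measures (week-12, week-26"). At each follow-up visit, the last included, participants "have the EMA app reinstalled on their phone to conduct the same EMA questions for 14-days", with the accelerometer worn over the same 14 days.
- **Outcome and test level**: the primary outcome is weight change across six months, and the Aim 1 analysis uses weight change at weeks 12 and 26. The Aim 2 section sets significance at p = 0.05.
- **Steps to reach the target** (Recruitment plans): existing links with weight management programmes will be used. No step to raise the rate, projection or revised target is given.

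**The concern.** The target, the closing dates and the accrual to date appear in one article and are not reconciled with each other. The end of data collection implies a latest useful enrolment date that the article does not state. Accrual so far is far below what that date would require, yet the sample size and power are presented unchanged.

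If the end date holds, the week-26 regressions will rest on a fraction of 50 participants, and a null result could be read against a power of 0.80 that the study never had. If recruitment instead runs late into 2026 and the end date still holds, the last enrollees will have no week-26 weight.

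**Working it through.** **Inputs from the article.** Recruitment start 7 March 2025; nine enrolled as of January 2026; target 50; end of data collection 28 February 2027; last visit at week 26; 14 days of data collection after it. The day in January is not given, so 1 to 31 January 2026 is taken as the range. A month is 30.44 days.

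**1. Latest useful enrolment date**
- Week-26 weight only: 28 Feb 2027 − 26 × 7 = 182 days → 30 August 2026.
- With the 14-day EMA and accelerometry: 28 Feb 2027 − (182 + 14) = 196 days → 16 August 2026.
- For comparison, week-12 weight: 28 Feb 2027 − 84 days → 6 December 2026.

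**2. Observed rate**
- 7 March 2025 to 1 January 2026 is 300 days (9.86 months): 9 / 9.86 = 0.91 per month.
- 7 March 2025 to 31 January 2026 is 330 days (10.84 months): 9 / 10.84 = 0.83 per month.

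**3. Projected total = 9 + rate × months remaining**

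| Close of enrolment | Snapshot 1 Jan | Snapshot 31 Jan |
|---|---|---|
| 16 Aug 2026 | 9 + 0.913 × 7.46 = 15.8 | 9 + 0.830 × 6.47 = 14.4 |
| 30 Aug 2026 | 9 + 0.913 × 7.92 = 16.2 | 9 + 0.830 × 6.93 = 14.8 |
| 31 Dec 2026 | 9 + 0.913 × 11.96 = 19.9 | 9 + 0.830 × 10.97 = 18.1 |

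Nine events give an imprecise rate. At the upper exact 95% Poisson limit (1.58 to 1.73 per month), the total by 16 August is still only 19 to 22, and by 31 December 26 to 30.

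**4. Rate needed for 50 (41 more)**
- By 16 August: 41 / 7.46 = 5.5 to 41 / 6.47 = 6.3 per month, which is 6.0 to 7.6 times the observed rate.
- By 30 August: 41 / 7.92 = 5.2 to 41 / 6.93 = 5.9 per month, which is 5.7 to 7.1 times.
- At the observed rate, 41 more would take 45 to 49 months, so 50 would be reached between late September 2029 and mid-March 2030.

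**5. Power.** The method is exact power for the overall R² test in regression with random predictors, reading the 0.3 effect size as R² = 0.30. The article's own figure comes first: n = 50, five predictors and alpha 0.01 give 0.77 with a critical R² of 0.283, against the stated 0.80 and 0.27. Those two values are met at n = 53. This small gap is a separate matter, but it shows that the calculation is close to the one the article used. At smaller n, with R² = 0.30 and five predictors:

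| n | alpha 0.01 (sample-size statement) | alpha 0.05 (analysis section) |
|---|---|---|
| 15 | 8% | 26% |
| 20 | 17% | 40% |
| 30 | 39% | 66% |
| 50 | 77% | 92% |

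**The case against.** **The dates do not contradict each other.** A reader might infer that the dates and the target are logically incompatible, or that the article plans to recruit to the end of December 2026. Neither is supported. The text says recruitment will conclude in 2026 without naming a month, and a close in mid-August satisfies both dates. The shortfall is a forecast from the observed rate. This objection stands, and it limits the point to that forecast and to the missing last-enrolment date.

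**Accrual may speed up.** Nine enrolments include the start-up period, and several programmes are named as sources. The article reports its progress openly. But it describes nothing that would support a rise of about six to eight times, and the upper Poisson limit stays far below 50.

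**The power loss depends on the test.** The figures at alpha 0.01 belong to the sample-size statement and should not be taken as the power of the planned analysis, which tests at 0.05. With only the two predictors named for hypothesis 1a (average and change frequency), power at 0.05 would be about 46%, 62% and 83% at n = 15, 20 and 30. All of these are for the overall R² test, not for the stress-variability coefficient. At n = 15, power is low in every version.

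**The model is not fixed at eight or more terms.** One can count that many from the list of covariates, but the article calls them potential and elsewhere allows up to five predictors. The point does not rest on model size.

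**Not all outcome data are lost.** Week-12 weight is also analysed, and anyone enrolled by 6 December 2026 would reach it before the end date. The article also plans to analyse all available data. This stands: the loss concerns week 26.

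**Conclusion.** The point holds as a projection. At 0.83 to 0.91 enrolments per month, about 14 to 16 participants would be enrolled in time to complete week 26 by 28 February 2027, against 50 stated. Enrolling until 31 December 2026 would give only 18 to 20, and those who joined after 30 August would have no week-26 weight by the end date. The stated n = 50 and 0.80 power are therefore not supported by the article's own progress figures. At n = 15, overall-test power with five predictors is about 8% at alpha 0.01 and 26% at 0.05.

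This assumes a constant rate, a January snapshot on any day of that month, an effect size read as R² = 0.30, and no loss to follow-up. The last assumption is favourable, because one of the nine has already been lost after the 3-month visit. The conclusion does not depend on the January day or on whether 26 or 28 weeks are counted. It would change only with an acceleration that the article does not describe.

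**What to change.** In Current progress, do one of two things:

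1. Keep 28 February 2027 and state a last-enrolment date that fits it: 16 August 2026 for the full protocol, or 30 August 2026 if only the week-26 weight must be complete.
2. Keep a later close of recruitment and move the end of data collection to 28 weeks after the last enrolment. A close on 31 December 2026, for example, gives 15 July 2027.

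Under either choice, restate in Sample size and power calculation the number of participants projected to have week-26 weight, with the power or detectable effect at that number and at the alpha to be used in the analysis. If 50 is kept, say what is expected to raise accrual to about 5 to 6 per month (first choice), or what later end date it implies (second choice).

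This is a change of text only. The cost is that the restated sample size and power are less favourable, or that the study ends later.

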## Discussion

This study aims to examine potential pathways of stress and stress-related concepts with subsequent weight change and health behaviors during a behavioral weight loss intervention. Utilizing mHealth technology, assessing various forms of stress and through multiple modalities, and assessments in parallel to a behavioral weight loss program may help improve our understanding from cross-sectional or singular stress measures. The resulting data will inform if a much-needed EMI can support individuals as they engage in behavioral weight loss program in the real-world for lasting impact. Pending study findings, there are three main areas for future exploration. First, future studies may include examining similar constructs and outcomes amongst individuals using obesity-management medications; these medications are becoming more common [54] but individuals using these medications are excluded from enrolling in this study. Second, other considerations for future study may be examining other mental health constructs (e.g., depressive symptomology). The current study utilizes multiple questionnaires that are highly correlated with depressive symptoms (e.g., Perceived Stress Scale [40]), but does not directly address this construct. Finally, consideration of amount, types, and use of coping mechanisms may still require further exploration. It is possible that an individual with high coping ability, and thus lower variability, may still result in positive health behavior (e.g., physical activity and adequate sleep) [5,8]. Use of coping mechanisms may also improve as individuals engage in a behavioral weight loss program [5]. The current study addresses this concern by collecting additional details on coping mechanisms used at the individual and daily level.

We will present our findings at local meetings and community events, including at the community-based weight management program at University of Kansas Medical Center. These efforts will increase awareness of the importance of stress and coping while making a behavior change, but also opportunities to change the home and local to facilitate adequate physical activity and sleep. We will present this information at the appropriate health literacy level and create informational flyers for adults and communities to utilize this information amongst their community. We will prepare a lay person handout of results and next steps to share with community partners who helped with recruitment, along with the flyers. The results from our study will have implications to identify potential pathways to improve stress and mental health for long-term behavior change and weight management success.

## Abbreviations

BMI: Body Mass Index
ELISA: Enzyme-linked immunosorbent assay
ENMO: Euclidian Norm Minus One
FCI: Food Cravings Inventory
FDA: Federal Drug Administration
EMA: Ecological Momentary Assessment
EMI: Ecological Momentary Intervention
MVPA: moderate-to-vigorous physical activity
PANAS: Positive and Negative Affect Scale
